#### 2.5.1 Recruitment, retention and adherence

Recruitment rate will be calculated as the percentage of participants enrolled as a function of the number of participants invited. Study retention will be calculated as the enrolled participants who complete all required parts of the study as a function of total enrolled participants. Tolerance will be defined as procedural adherence for each methodology, whereby completion of each of the various measurement and intervention components will be carefully considered for planning of future interventions. The acceptability of physiotherapy intervention frequency of twice per week will be assessed based on attendance and family feedback.

#### 2.5.2 Safety

Potential risks for Trexo physiotherapy may include the usual risk of muscle soreness when doing walking-based activities, skin irritation from the exoskeleton’s shin cuffs or other parts of the Trexo’s walking frame, or falling when transitioning child in/out of the Trexo device. Of note, there were no adverse events documented during a 3-month case study of Trexo use at home and in the community (Diot et al., 2021).

To support close monitoring of any negative physical impacts associated with Trexo use, the treating PT will document the presence of any skin irritation experienced by the participant before and immediately after each treatment session. If pain is indicated by the child, the PT will check the identified area for bruising, redness or other skin/tenderness issues that might be associated with exoskeleton wear and/or the previous Trexo session. The child’s own method of discomfort/pain communication will be taken into account when quantifying the discomfort. Body location, discomfort type (muscle vs. skin), severity (mild to severe), duration (temporary vs. sustained) of pain will be tracked thoroughly, with recommendations made for next steps (section “2.10 Adverse events”). These safety categories will be summarized when assessing the acceptability of the Trexo intervention.

#### 2.5.3 Session tracking and documentation

All of the Trexo-based physiotherapy sessions will have associated content summary sheets (completed by the treating PT) that will permit systematic documentation of motor tasks undertaken, successes, challenges, adjustments, strategies applied, and next session planning. Additionally, a non-PT member of the research team will document the following at each session: attending staff roles, extra equipment/props used, Trexo setup time, Trexo tablet modes used, changes to range of motion or robotic support force, physical adjustments, walking and standing activities, total step count and walking time, timing and rationale for all session pauses (i.e. rest, adjustment, discomfort, standing activity), socialization opportunities, child communication modes, and observable fatigue (Supplementary Material 1).

Documentation of the active ingredients of PT interventions using exoskeleton treatments (i.e., device parameter changes and activities undertaken) has been largely missing in the literature to date. There is strong advocacy now to include tracking and reporting of device usage parameters in future trials to aid in the understanding of how best to apply the technology and better support the translation of best practice protocols into clinical practice (Cherni and Ziane, 2022; van Dellen and Labruyère, 2022). Thus, one session per child (the 10*^th^* or 11*^th^*) will be videorecorded to allow documentation of the extent to which motor learning approaches were taken by the PT/PTA team, assessed by an external rater using the *Motor Learning Strategies Rating Instrument* (MLSRI; Spivak et al., 2021).

#### 2.5.4 Child, parent, and physiotherapy team satisfaction

At the end of each session, child-rated Trexo session satisfaction will be assessed using a picture-format (smiley-o-meter based) rating scale (Zaman et al., 2013). The child will be given picture scales formatted as a choice of a happy/neutral/sad face to rate how they felt in the Trexo (comfort), level of exertion (tiredness at end of session), and their level of enjoyment for each of the Trexo activities done. Summaries of each experience category (comfort, tiredness, task enjoyment) will be quantified across all 12 sessions for each participant.

Optional qualitative interviews will capture parent and PT/PTA team perspectives on the Trexo use with the child (section “2.7.2 Postural control assessments”). This will be an opportunity to solicit feedback on study design, tolerance, and opinions on different study aspects from a clinical and family perspective. PT/PTA teams will have the opportunity to reflect on the Trexo training process and the rollout of the intervention itself, so that this process can be optimized for future PT/PTA cohorts.

### 2.6 Primary study outcomes

Primary study outcomes will be assessed at multiple timepoints (Table 2) pre- and post-intervention.

**TABLE 2 T2:** Outcome measures across timepoints.

		Timepoint			
Measures	Completed by	O_0_	X	O_1_	O_2_
**Primary outcome measure**					
GMFM-88*	PT assessor	•		•	•
COPM *	Parent with PT assessor	•		•	•
GAS	Treating PT/PTA		**T** (†); **T** (‡)		
MRI	SR with MRI technician	•		•	•
MMG	SR		**T, W** (†); **T, W** (‡)		
**Secondary outcome measure**					
ROM and Tardieu Spasticity*	PT assessor	•		•	•
PPAS and LSS*	PT assessor	•		•	•
PEDI-CAT*	Parent	•		•	•
1WT and DMA	Treating PT/PTA		**T, W** (†); **T, W** (‡)		
Heart rate	SR		**T, W** (‡)		
**Participant characterization**					
MACS*	PT assessor with parent	•			
CFCS	Treating PT and SR			**T**	
Dimensions of mastery*	Parent	•			
Trexo physical adjustments	Treating PT and SR		**T**		
**PT and parent perspectives**					
Parent baseline interview	Parent with SI		•		
Parent outcomes interview	Parent with SI			•	
PT training interview	Treating PT/PTA with SI			•	
PT outcomes interview	Treating PT/PTA with SI			•	

*Completed during motor/functional assessment visit. **T** = done in Trexo; **W** = done in regular walker; • = done without any device. (†) denotes the beginning of the intervention phase and (‡) denotes the end of the intervention phase.

#### 2.6.1 Gross motor skills

The *Gross Motor Function Measure* (GMFM-88; Russell et al., 2000) will be administered by an independent PT assessor during the motor/functional assessment at baseline and immediately post-intervention. It will also be used 1-month post-intervention to gauge maintenance/progression of any functional gains. PT assessors will be trained on the GMFM-88 and all other PT assessment measures by the study’s co-principal investigator prior to their first study assessment. All PTs will already have extensive clinical experience administering the GMFM with children with CP, and variable experience with the other measures. The full 88-item version of the GMFM will be used as it more comprehensively captures a range of abilities in its lowest dimensions (Lie/Roll and Sit) than the abbreviated GMFM-66. This will be important as better trunk and head control are anticipated to be goals and potential outcomes associated with Trexo use in children in GMFCS Level IV. The GMFM-88 testing will be captured on video to enable post-assessment review by PTs. Pre/post change scores will be calculated with descriptive statistics representing results of the group. The GMFM has excellent test-retest reliability (Bjornson et al., 1998), and responsiveness to change (Vos-Vromans et al., 2005).

#### 2.6.2 Functional priority goals

The PT assessor will guide the attending parent(s) through the *Canadian Occupational Performance Measure* (COPM; Law et al., 1990) during the baseline functional assessment visit to set priority outcome goals for their child. These 3–4 goals will be guided from a menu prepared by the investigators of walking-based or other functional outcomes that may arise from Trexo use. These goals can relate to the child’s abilities in home, school, or community environments. The parent(s) will use the COPM’s 10-point response scales to rate the importance of each goal, as well as satisfaction and performance of each at baseline. COPM goals will be rated by the parent(s) again at the post-intervention assessment, as well as the 1-month post intervention assessment. All efforts will be made to have the same parent attend each assessment to maintain consistency. The parent(s) and assessor will be blinded to previous COPM scores. Pre/post mean change scores will be calculated for each child. The COPM has been adapted for use with children and has demonstrated strong internal consistency, construct validity, and responsiveness to change (Cusick et al., 2007).

*Goal Attainment Scaling* (GAS) goals and achievement levels will be set by the treating PTs, and will be Trexo-directed or regular walker-associated. GAS will serve as an individualized measure of change for each child and will link to the parent-chosen COPM goals to allow evaluation of the targeted subcomponents of COPM’s higher level functional priority goals (King et al., 2000; Ostensjo et al., 2008). These two or three goals will be set by the 3*^rd^* physiotherapy session, allowing the PT team to first form a realistic idea of the child’s functional abilities and potential areas of improvement. GAS outcomes will be scored per goal by the child’s treating PT upon completion of the child’s last physiotherapy session, and a summary T-score will also be calculated. GAS is commonly used with children with CP who use walkers, and has demonstrated strong internal consistency, construct validity, and responsiveness to change (Paleg and Livingstone, 2016).

#### 2.6.3 Neuroimaging

Awake magnetic resonance imaging (MRI) head scanning will be done in the Siemens Prisma MAGNETOM 3-Tesla MRI scanner with a 36-channel head coil at Holland Bloorview Kids Rehabilitation Hospital (Figure 4). If tolerated, these will be done at baseline and immediately post-intervention, with an option for a third scan 1-month post-intervention. Prior to the baseline scan, families will be provided with MRI resources intended to prepare and educate them for an awake scan with their child. Resources include a child-friendly MRI explanation book, video links to a tour of the center’s MRI suite, links to MRI cartoons, links to MRI sound samples, and a link to the resting state fMRI video. This is meant to ease any apprehension or stress associated with the MRI process.

**FIGURE 4 F4:**
[figure not shown]
The MRI suite at Holland Bloorview Kids Rehabilitation Hospital (Toronto, Canada). This suite is fully accessible, child-friendly, research-focused, immersive, and customizable. Awake MRI head scanning occurs pre- and post-intervention.

Total MRI acquisition time will be kept under 40 min for this young demographic. MRI scanning will include T1-weighted scanning, T2-weighted scanning for incidental findings, diffusion kurtosis imaging (DKI), and resting state functional MRI (fMRI) (scan parameters: Supplementary Material 2). Participants will wear noise-canceling headphones and watch videos of their choice during the structural scans, and the visual paradigm Inscapes video (headspacestudios.org/inscapes) during the fMRI scan. Incidental reviews of all scans will be completed by a pediatric radiologist.

#### 2.6.4 Muscle recordings

Mechanomyography (MMG) muscle recordings (Plewa et al., 2017) from each child will be recorded at baseline and post-intervention, concurrently with walking assessments (section “2.8.3 Motivation-related traits”) in their regular maximum support walker (if they have one) and the Trexo walker.

Bilateral MMG data will be collected using tri-axial ADXL335 accelerometers (2.0 cm x 1.5cm; sampling rate 1000 hz/channel), powered by a 3.3V regulator. 8 accelerometers will be placed on muscle sites bilaterally to record muscle vibrations: erector spinae (longissimus thoracis), biceps femoris, vastus lateralis and gluteus maximus. These muscles were selected based on their role in gait (Hesse and Uhlenbrock, 2000; Jonkers et al., 2003; Sousa and Tavares, 2012; Di Nardo et al., 2015) and body surface accessibility for muscle sensors while in the Trexo. Accelerometers will be attached with medical tape on the skin above the largest part of the muscle belly (Figure 5). All selected muscle sites are above the knee as Trexo shin cuffs preclude access to below-knee locations. An additional (9^th^) sensor will be attached to the knee joint of the Trexo device to record robotic leg movement.

**FIGURE 5 F5:**
[figure not shown]
Mechanomyography sensor layout, shown on the right side of the body. Target muscles include vastus lateralis, biceps femoris (long head), gluteus maximus, and erector spinae (longissimus thoracis). Sensors will be secured on top of the skin with medical tape and located according to origin and insertion points of the muscles.

Each accelerometer will be wired to a data collection unit comprised of two National Instruments USB-6210 data acquisition cards. The data acquisition cards will plug into a laptop computer via USB, which will be fitted into a backpack that travels with the walkers (hung on the back of the Trexo or carried by a member of the research team). A second computer will connect remotely to the laptop, allowing the researcher to start and stop the data collection as well as remotely mark the data in real time during significant events (e.g., pauses for adjustments, start/stop of walking assessments).

MMG data collection will take place in 25-min testing sessions (including setup; per walker) that will encompass the 1-min walk and dynamic mobility assessment (section “2.7.4 Gait assessments”) followed by a free (unstructured) walking period with the child. Each participant will walk for a minimum of 5 min (or until fatigue to a maximum of 20 min) in their regular maximum support walker and the Trexo exoskeleton. Baseline MMG readings will be taken during quiet standing for 30 s at the start of each testing session – these readings will be used to normalize signals.

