i)Assess aspects of clinical feasibility, safety, and acceptability of Trexo gait training within an outpatient center and schoolii)Capture the Trexo user experience of children and physiotherapists during exoskeleton gait training, as well as physiotherapists’ and parents’ perspectives of outcomes associated with useiii)Assess motor and functional outcomes pre/post Trexo gait training (including any carryover effects)iv)Examine brain anatomy and brain connectivity pre/post Trexo gait trainingv)Evaluate muscle activations, particularly indicating muscle fatigue, during Trexo gait training (compare with muscle activations during use of regular assistive mobility devices)vi)Capture heart rate and heart rate variability during Trexo gait training (compare with heart rate during use of regular assistive mobility devices).

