#### 2.7.4 Gait assessments

Functional gait will be assessed via a *1-minute walk test* (1MWT) (Hassani et al., 2014) and the *Directional Mobility Assessment* (DMA) (Wright and Jutai, 2006; Livingstone and Paleg, 2016), done in the child’s regular walking device (if they use one) and the Trexo walker. The 1MWT will measure the distance walked down a straight wide hallway within 60 s with the Trexo and with the child’s regular walker, with support from the child’s PT/PTA team as needed for steering (Trexo and regular walker) and facilitating steps (regular walker). The DMA incorporates a functional walking course: straight walking, turns, obstacles, narrow path, and backing up.

These walking tasks will be administered by the child’s treating PT/PTA simultaneously during MMG/heart rate monitoring (facilitated by study researchers). Involvement of the PT/PTA in this testing is essential as they are Trexo-trained and aware of the child’s functional abilities and safety considerations. A video recording will be made of these walking tests to permit their rating by an independent PT assessor to maintain independence of scoring from the clinical team.

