*MMG* signals will be calculated as the magnitude of the vector sum of the tri-axial ADXL335 accelerations. Data will be segmented according to periods of activity and normalized to the initial period of quiet standing for each participant. Accelerometer data will be processed using Matlab Software (Natick, Massachusetts: The MathWorks Inc.): bandpass filtered between 5 and 100 Hz (4^th^ order Butterworth filter) and processed with a symlet wavelet transform (Alves and Chau, 2010; Achmamad and Jbari, 2020). Device-induced noise will be compared in the Trexo and the child’s regular walker. Heel strike will be identified based on video recordings to demarcate phases of the gait cycle and changes in magnitude and slope of the force. We will extract and select features in time, frequency, and time-frequency domain for classification.

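### Each MMG session ends in unstructured walking and repeats no standard task late, so a fresh-versus-fatigued comparison across the session mixes task with time

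*Protocol article*

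**What the plan says.** The protocol article lists MMG among the primary outcome measures (Table 2, section 2.6.4). It is recorded at the start and end of the intervention phase, in the Trexo and, for children who have one, in the regular walker. Objective (v) in the Introduction is to "Evaluate muscle activations, particularly indicating muscle fatigue, during Trexo gait training", compared with the usual device.

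Section 2.6.4 sets out the session:

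- Length: "MMG data collection will take place in 25-min testing sessions (including setup; per walker").
- Structured part: a session "that will encompass the 1-min walk and dynamic mobility assessment". No order between these two is stated. I take the second to be the DMA of section 2.7.4, to which the text cross-refers.
- Last part: the structured tasks are "followed by a free (unstructured) walking period with the child".
- Walking time: "Each participant will walk for a minimum of 5 min (or until fatigue to a maximum of 20 min"), in each device.
- Reference reading: 30 seconds of quiet standing at the start of the session.

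The tasks differ in content. In section 2.7.4 the 1-minute walk is along a straight hallway, whereas "The DMA incorporates a functional walking course: straight walking, turns, obstacles, narrow path, and backing up".

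On analysis, section 2.11.1 says "Data will be segmented according to periods of activity", and section 2.6.4 lets the researcher "remotely mark the data in real time during significant events (e.g., pauses for adjustments, start/stop of walking assessments").

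**The concern.** Within a session, fatigue would show as a change in the muscle signal between early and late walking. To read it cleanly, the child should be doing the same thing at both points. In the sequence described, everything standardised happens early and everything late is unstructured. A change between the two parts could reflect tiring, or a different speed, path, amount of turning or number of pauses.

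This concerns data collection and is not a missing analysis detail. The fatigue metric may well be defined in a fuller document, and its absence from an article is no fault. But if no standard task is recorded late, no later analysis plan can supply one.

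At stake is how well the study can answer the fatigue part of objective (v). The Discussion hopes that muscle and heart-rate data can help establish training limits, especially for nonverbal children, so a task effect read as fatigue would be unhelpful there.

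**Working it through.** The protocol gives no effect size, SD, alpha or power for MMG, so there is no figure to reproduce. The check asks how closely task is tied to elapsed time, and what a pooled trend would show if there were no fatigue.

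**Inputs**
- Total walking time T: 5 to 20 minutes (section 2.6.4), read as covering the structured tasks and the free walk together.
- Structured time s: 2 to 4 minutes. This is an assumption, because the DMA's duration is not given.
- Structured share p = s/T.

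**Formulas**

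Let t be elapsed walking time, uniform on 0 to T. Let g be 0 during structured tasks and 1 during free walking. Then:
- var(t) = T²/12, var(g) = p(1−p), cov(t, g) = T·p(1−p)/2.
- Correlation r = √(3p(1−p)).
- Variance inflation VIF = 1/(1−r²).
- Suppose the signal differs by one unit between tasks and there is no fatigue. A straight line fitted over the session shows a start-to-end change of T·cov/var(t) = 6p(1−p) units.

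**Results**

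| T (min) | s (min) | Free walk (min) | r | VIF | False change per unit task step |
|---|---|---|---|---|---|
| 5 | 2 | 3 | 0.85 | 3.57 | 1.44 |
| 5 | 3 | 2 | 0.85 | 3.57 | 1.44 |
| 5 | 4 | 1 | 0.69 | 1.92 | 0.96 |
| 10 | 2 | 8 | 0.69 | 1.92 | 0.96 |
| 10 | 3 | 7 | 0.79 | 2.70 | 1.26 |
| 10 | 4 | 6 | 0.85 | 3.57 | 1.44 |
| 20 | 2 | 18 | 0.52 | 1.37 | 0.54 |
| 20 | 3 | 17 | 0.62 | 1.62 | 0.77 |
| 20 | 4 | 16 | 0.69 | 1.92 | 0.96 |

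Example, T = 5 and s = 2: p = 0.4, r = √(3 × 0.4 × 0.6) = √0.72 = 0.85, VIF = 1/0.28 = 3.57, false change = 6 × 0.24 = 1.44. Between grid points the ceiling is at p = 0.5, where r = √0.75 = 0.87, VIF = 4 and the false change is 1.5.

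A plain difference between a structured segment and a late free-walk segment carries the whole task step, that is, 1 unit.

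**Within free walking only.** The same fit gives a false change of 0, because the task step lies outside the segment. That zero assumes constant activity within the segment, which an unstructured walk does not secure. The segment lasts 1 to 3 minutes when a child walks the 5-minute minimum and 16 to 18 minutes at the 20-minute maximum.

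**Sensitivity to the reading of walking time.** If the 5-minute minimum applies to free walking alone, the short-segment problem eases. The pooled-trend problem does not: with s = 2 to 4, p runs from 2/7 to 4/9, and 6p(1−p) from 1.22 to 1.48.

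**The case against.** The strongest reply is that the faulty comparison is not in the plan. Nothing says that fatigue will be read by setting early tasks against late ones. Task boundaries are marked in real time, the data are segmented by activity, heel strike is identified from video, and features in the time and frequency domains are extracted. A trend within one segment carries none of the between-task step. This stands, and it is why the limitation is modest. It does not remove it, because the segment left for that trend has no set pace or path and is shortest in the children who walk least.

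Four stronger readings are tempting, and the documents do not support them.

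- *Task and time are wholly confounded.* They are not: the correlation is below 1, and segmentation permits a within-segment trend.
- *The 1-minute walk always comes first and is the only standard straight walking.* Section 2.6.4 joins the two structured tasks without ordering them, and the DMA course itself contains straight walking. Only the free walk is fixed last.
- *The fixed sequence biases Trexo against the regular walker.* The sequence is the same in both, so order alone does not. Bias needs a task effect that differs by device. That is plausible, since the Trexo legs are powered and steps in the regular walker are facilitated as needed, but the documents do not quantify it.
- *A false-positive rate can be attached.* No early-versus-late test of MMG is planned, and the 10 children are justified by descriptive statistics and graphs. Any such rate would rest on a test and inputs that the protocol does not contain.

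It is also fair that a repeat has practical limits. Walking may stop at fatigue, so the final minute is not known in advance, and a tired child of 3 to 6 years may not complete it.

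**Conclusion.** The point holds as a modest limitation for objective (v). Structured tasks always precede unstructured walking, and no standard task is repeated late, so a fresh-versus-fatigued comparison across the session mixes task with time. A pooled trend would carry roughly 0.5 to 1.5 times whatever task difference exists. The size of that difference is unknown, so the size of any actual error is unknown too. The range rests on the assumed 2 to 4 minutes of structured tasks and on elapsed walking time being spread evenly. The trend within free walking is a usable but weaker alternative, least informative in short walks. For a descriptive feasibility study this calls for an inexpensive improvement to the procedure; it is no ground for discarding the MMG outcome.

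**What to change.** In section 2.6.4, add a repeat of a short standard straight hallway walk late in the free-walking period, within the existing walking time and as tolerated by the child. For example, do it at a preset time and, where possible, again near the end. Apply it in each device and at both time points, with the same event marking as the first walk.

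State that fatigue will be read from the within-child change between the first and the repeated straight walk, with the trend within free walking as support, and that structured segments will not be compared with free-walk segments for this purpose.

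Cost: no added visit, staff, equipment or walking time. There is slightly less unstructured walking, and some repeats will be missing in children who stop early. Report the number missing by device and time point, because those may be the children who tire soonest.
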